#### Anthropometry

Height and weight are measured using standard procedures. Height is measured to the nearest 0.1 cm using a portable stadiometer. Weight is measured to the nearest 0.1 kg using digital scales; children will wear school uniform (shoes removed).

#### Tolerance of Risk in Play Scale (TRiPS)

We are developing and testing the validity and reliability of data gathered with an instrument to examine adults' tolerances of risk during children's play. The scale is based on a Norwegian model of risky play [63]. We will collect data from 100 parents and teachers of children aged 3 to 13 years.

#### Qualitative data

Qualitative data in the form of audio recordings of risk reframing sessions, brief, written participant evaluations, and in-depth interviews with selected teacher and parent volunteers are gathered to understand some of the experiences and observations of the adults participating in the study.

#### Data analysis

Primary outcomes (activity levels) will be analysed using intention-to-treat principles. The effectiveness of the intervention for increasing activity, changing social skills and after school activities will be measured at both cluster and individual levels. Mixed-effects multi-level regression (STATA/IC 12, http://www.stata.com), taking clustering and repeated measurement of participants into account, will be used to examine net change from baseline values between groups. At the individual level, multivariate regression will be used to examine the contributions of activity level to changes in self-concept and social skills between groups. Secondary analyses will be conducted to explore subgroup effects (e.g., by sex). In addition, the contribution of potential confounders such as BMI will be explored.

Data from the audio recordings of the risk reframing sessions, parent interviews and field notes kept by project staff will be transcribed either in their entirety or as brief written reports. The resulting qualitative data will be converted to text to be analysed according to an adaptation of Charmaz's [64] approach to social analysis. Initial emergent themes will be identified and data coded for patterns and complexity regarding participants' experiences, actions, beliefs or relationships to risk, assumptions regarding risk, the larger process of which this action or belief is a part, and possible implications of such actions or beliefs for particular actors, institutional forms, parents, families, or children.

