**Methods/Design:**

This study protocol describes the design of a 3-year cluster randomised controlled trial (CRCT), in which schools are the clusters. The study consists of a 13-week intervention and 1 week each of pre-and post-testing. We are recruiting 12 schools (6 control; 6 intervention), with 18 randomly chosen participants aged 5 to 7 years in each school. The two intervention strategies are: (1) Child-based intervention: Unstructured materials with no obvious play value introduced to the playground; and (2) Adult-based intervention: Risk reframing sessions held with parents and teachers with the aim of exploring the benefits of allowing children to engage in activities with uncertain outcomes. The primary outcome of the study, physical activity as measured by accelerometer counts, is assessed at baseline and post-intervention. Additional assessments include social skills and interactions, self-concept, after school time use and anthropometric data. Qualitative data (i.e., transcriptions of audio recordings from the risk reframing sessions and of interviews with selected teacher and parent volunteers) are analysed to understand their perceptions of risk in play. The control schools have recess as usual. In addition to outcome evaluation, regular process evaluation sessions are held to monitor fidelity to the treatment.

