### Sample size

Sample size calculation involves deciding on both the number of schools (clusters) and number of children per school. The desired number of schools provides sufficient cluster-level data for subsequent analyses but, at the same time, is manageable in terms of implementation and data collection. We have selected 12 schools (6 control, 6 intervention) to meet these criteria.

The number of children needed per school is estimated by considering the amount of change from the intervention and correcting for the possibility that children at the same school affect one another's activity levels (determined by intra-cluster correlation [ICC]) We estimated the effect size from the intervention conservatively at 0.5 standard deviations (SD) based on a report that young children engage in moderate to vigorous playground activity 26% of the time and that 40% would be a realistic health-promoting target [57].

With *p *= 0.05, power = 80% and an ICC of .04, we require 18 children per school to show that an effect size of 0.5 SD is significant between groups. This reflects a 68% inflation in sample size over the number that would be required if no adjustment were made for cluster effect (64 vs. 108 participants/group).

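### Comparing net change from baseline is valid but less precise than adjusting post-test activity for the child's baseline, which the trial already measures

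*Protocol article*

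**What the plan says.** Under Data analysis, the protocol article plans a mixed-effects multilevel regression, "taking clustering and repeated measurement of participants into account", which "will be used to examine net change from baseline values between groups". It does not say that baseline activity enters as a covariate or that the two arms share a common baseline mean. BMI is the only covariate it names, as a potential confounder.

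There are two measurement waves. The abstract states: "The primary outcome of the study, physical activity as measured by accelerometer counts, is assessed at baseline and post-intervention". Table 1 schedules five days of accelerometry at each wave. The Randomisation section has baseline data collected before a school learns its allocation.

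The Sample size section sets p = 0.05, "power = 80% and an ICC of .04, we require 18 children per school", for an effect of 0.5 SD, and reports the cluster inflation as "64 vs. 108 participants/group". That calculation uses the plain outcome SD and no baseline correlation.

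**The concern.** A difference in change subtracts the whole baseline difference between arms, which amounts to assuming a slope of 1 of post-test on baseline. When the true slope is smaller, this over-corrects for chance imbalance and adds noise. Regression on baseline estimates the slope instead.

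Precision is scarce with 12 schools. At ICC 0.04 the baseline difference between arms has a standard deviation of about 0.18 SD by chance alone (derived in the working). The baseline data are already being collected, so precision lost through the choice of contrast is lost for nothing. Calling the analysis a mixed model does not remove the loss: with two waves and complete data, the group-by-time term is the difference in mean change.

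**Working it through.** **Inputs from the protocol.** 6 + 6 schools, 18 children per school, ICC 0.04, effect 0.5 SD, p = 0.05 (taken as two-sided), power 80%. **Assumed:** r, which the protocol does not give, shown over a range.

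**1. The protocol's own figure.** A two-sample t-test for 0.5 SD needs 64 per group. The design effect is 1 + 17 × 0.04 = 1.68, and 64 × 1.68 = 107.5, so 108 = 6 × 18. The figure reproduces. It has the variance of a follow-up-only comparison.

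**2. Standard error, follow-up only.** Variance = (2/6)(0.04 + 0.96/18) = 0.0311, so SE = 0.176 SD. The chance baseline difference between arms has the same SD.

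**3. Is the mixed model a change score?** A model with group, time and group × time, fitted to one simulated complete data set, gave a group × time estimate of 0.7621. The simple difference in mean change was also 0.7621.

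**4. Variance relative to follow-up only.** Change: 2(1 − r). Baseline-adjusted: about 1 − r². The difference is 2(1 − r) − (1 − r²) = (1 − r)², positive for every r below 1. The ratio of change to adjusted is 2/(1 + r).

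| r | change | adjusted | ratio |
|---|---|---|---|
| 0.3 | 1.40 | 0.91 | 1.54 |
| 0.5 | 1.00 | 0.75 | 1.33 |
| 0.7 | 0.60 | 0.51 | 1.18 |
| 0.9 | 0.20 | 0.19 | 1.05 |

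Change exceeds 1, and so is worse than ignoring baseline, only when r is below 0.5.

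**5. Power for 0.5 SD on a t reference.** Simulated with 12 schools × 18 children, ICC 0.04 and the same r at school and child level:

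| r | change | child baseline as covariate | school-mean baseline added |
|---|---|---|---|
| 0.3 | 57% | 76% | 70% |
| 0.5 | 73% | 84% | 79% |
| 0.7 | 91% | 94% | 91% |

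Noncentral t agrees for change (58.0%, 72.4%, 90.8% on 10 df) and for adjustment (75.3%, 82.9%, 94.1% on 9 df). Follow-up only gives 72.4% on 10 df, against 80.9% by the normal approximation.

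**6. Why the school-mean term costs so much.** It makes the group effect an analysis of covariance on 12 school means, and estimating that slope inflates the variance by about 1 + 1/8 = 1.125. Then 1.125(1 − r²) exceeds 2(1 − r) when 1.125(1 + r) > 2, that is, when r is above about 0.78. Of the gain over change, it keeps 13 of 19 points at r = 0.3, 6 of 11 at 0.5 and none at 0.7.

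**7. If schools and children differ in stability.** Let p be the correlation over time of school effects and s that of children within schools. Then r = (18 × 0.04p + 0.96s)/1.68 = 0.429p + 0.571s. With child-level slope s, the adjusted variance is 1 − 2sr + s². This is below 2(1 − r) when |s − r| < 1 − r. For s below r that means r < (1 + s)/2, or 0.429p + 0.071s < 0.5, which is true unless p = s = 1. For s at or above r it holds whenever s is below 1. Simulated SEs for change and adjusted agree: 0.200 and 0.166 (r = 0.33), 0.165 and 0.148 (r = 0.57), 0.142 and 0.131 (r = 0.69).

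**The case against.** The strongest case against has four parts.

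- **The wording is one condensed sentence in an article.** A mixed model that accounts for repeated measurement is compatible with a common-baseline longitudinal model, and such detail often sits in the analysis plan. In part this stands: the sentence does not exclude that model. But it does fix the contrast as net change, and the ordinary fit of that contrast is the change score.
- **The change analysis is not wrong.** This stands. It is unbiased under randomisation, and the over-correction describes results given a chance imbalance. A reader might infer that the planned analysis is biased or the sample size miscalculated. Neither follows: 64 and 108 reproduce.
- **The loss may be small.** This stands. Nothing in the protocol shows that r is below 0.5. The relevant r is that of school means, which can exceed the child-level value (a child-level 0.42 gave 0.57 in simulation), and averaging five days would tend to raise it. A reader might infer that the trial will do worse than if it ignored baseline; the documents support only that it could.
- **Adjustment is not always better.** This stands for one form of it. A separate school-mean baseline term loses to change at r of 0.8 or above. It does not stand for the child's baseline value, which beat change at every r simulated from 0.2 to 0.9.

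A reader might also take the 73% at r = 0.5 as the price of change scores. It is not. At r = 0.5 the change analysis has exactly the variance the sample size assumed, and follow-up only also gives about 72%. That shortfall from 80% comes from the t reference with 12 clusters.

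**Conclusion.** The concern holds as a matter of efficiency. The stated contrast is valid but less precise than adjusting for the child's baseline, by a variance factor of 2/(1 + r). The cost in power is about 19 points at r = 0.3, 11 at 0.5 and 3 at 0.7, and it is negligible above about 0.8. Being worse than ignoring baseline is conditional on a school-mean r below 0.5.

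The power figures assume ICC 0.04, 18 children in every school, complete data and the same r at both levels. The ordering in favour of child-baseline adjustment survives unequal r at ICC 0.04. It is not guaranteed if the true ICC is much larger and schools are far more stable over time than children; the constrained longitudinal model is then the safer of the two remedies.

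**What to change.** Replace the net-change wording for the primary outcome with a sentence such as: The primary analysis is a mixed model of post-test activity on group and the child's baseline activity, with a school random effect. An acceptable alternative is a constrained longitudinal model with a common baseline mean in both arms and random effects for school, school-by-time and child. Choose one before outcome data are seen.

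Do not add a separate school-mean baseline term to the primary model. Report net change by arm descriptively. Treat the SSIS-RS and PSPCSAYC scores, which are also measured at both waves, in the same way.

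The cost is one sentence of analysis text. No further data are needed and the sample size is unchanged.

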### Outcome measures

The primary outcome measure is children's physical activity, as measured by accelerometers. The secondary outcomes include: self-concept and social skills, social interactions, after school time use and anthropometric measures. All the measurements are performed during one full school week (Table 1).

**Table 1 T1:** Outcome measures and schedule of the study

Outcome	Measure	Data collection	Dependent variable	Baseline	Post-test
BMI	*Stadiometer and scales*	Researcher with child	Height and weight	1 occasion	1 occasion
Physical Activity	*Actigraph accelerometer^1^*	Devices worn by children	Counts, and minutes in sedentary and moderate to vigorous activity	5 days	5 days
	*Activity Diary^2^*	Palm pilots responded on by parents	Activities undertaken after school	4 days	4 days
Social Interaction	*Playground Behaviour*	Video recording	Social behaviour	15 min	15 min
	*SSIS-RS ^3^*	Parent and teacher reports	Social skills and problem behaviour	1 occasion	1 occasion
Self-concept	*PSPCSAYC^4^*	Researcher with child, and teacher reports	Feelings of competence	1 occasion	1 occasion

^1 ^www.theactigraph.com

^2 ^Palm pilot Z22

^3 ^Social Skills Improvement System Rating Scales [61]

^4 ^Pictorial Scale of Perceived Competence and Social Acceptance for Young Children [60]

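### Self-concept is named only under an individual-level regression with no stated school level; a group term in that model would have a standard error that is too small

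*Protocol article*

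**What the plan says.** The Data analysis section of the protocol article describes two quantitative analyses.

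- **Effectiveness.** Activity, social skills and after-school activities are to be assessed at cluster and individual level. A mixed-effects multilevel regression, which allows for clustering and for repeated measurements on the same child, compares change from baseline between the arms.
- **Contribution of activity.** The next sentence names another method: "At the individual level, multivariate regression will be used to examine the contributions of activity level to changes in self-concept and social skills". It ends by relating those changes to the comparison between groups. It mentions neither school nor clustering.

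The Outcome measures section lists self-concept as a secondary outcome alongside social skills. In Data analysis, social skills appear under both methods and self-concept only under the second.

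The Sample size section treats within-school dependence as material. It describes the calculation as "correcting for the possibility that children at the same school affect one another's activity levels" and concludes: "With *p *= 0.05, power = 80% and an ICC of .04, we require 18 children per school". On the number of schools it says: "We have selected 12 schools (6 control, 6 intervention) to meet these criteria".

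**The concern.** Schools are randomised, not children. A comparison of the arms therefore has to carry the between-school variation, whichever outcome is compared. The protocol does this in its first model. It then names a different method and a different level for the only analysis that mentions self-concept.

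This is more than a detail left unsaid. A method and a level of analysis are stated, directly after a sentence that ties clustering to the other method. An analyst who follows the text literally would fit about 216 children (12 × 18) as independent observations and could report a group difference in self-concept from that fit.

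At stake is the false-positive rate for a named secondary outcome. The Background links self-concept to being bullied less and to being included in play, so a spurious group difference here would feed the project's wider claims.

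**Working it through.** **Inputs, all from Sample size unless noted**

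- Effect size 0.5 SD, alpha 0.05, power 80%. Sidedness is not stated; two-sided reproduces the printed figure.
- School ICC 0.04, stated for activity only.
- 12 schools, 6 per arm, m = 18 children per school. Child selection gives a consent target of 20.

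**Step 1: reproduce the plan's own figure**

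- Two-sample comparison of means at 0.5 SD: the t-based calculation gives 63.8, so 64 per group (the normal approximation gives 63).
- Design effect = 1 + (m − 1) × ICC = 1 + 17 × 0.04 = 1.68.
- 64 × 1.68 = 107.5, rounded up to 108 = 6 × 18.

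The printed 64, 108 and 68% are all recovered, so 1.68 is the protocol's own measure of how much clustering matters.

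**Step 2: leave the school level out of a group contrast**

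- Correct SE / naive SE = √(design effect) = √1.68 = 1.296.
- Shortfall of the naive SE = 1 − 1/1.296 = 0.228, about 23%.
- Actual type I error of a nominal 5% test = 2 × [1 − Φ(1.96 / 1.296)] = 0.1305, about 13%.

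A simulation of 6 + 6 schools with 18 children each (20,000 runs, ICC 0.04, no true effect) gave 0.128 for the naive test. A t-test on the 12 school means (10 degrees of freedom) gave 0.048.

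**Step 3: range**

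The documents give no ICC for self-concept or social skills. All rows except the 0.04 rows use assumed ICCs, and using 0.04 for these scales is itself borrowed from activity.

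| m | ICC | Design effect | SE ratio | Naive SE too small by | Type I error |
|---|---|---|---|---|---|
| 18 | 0.01 | 1.17 | 1.082 | 7.5% | 7.0% |
| 18 | 0.04 | 1.68 | 1.296 | 22.8% | 13.1% |
| 18 | 0.10 | 2.70 | 1.643 | 39.1% | 23.3% |
| 20 | 0.04 | 1.76 | 1.327 | 24.6% | 14.0% |

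**Step 4: where the figures apply**

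They apply to a term that is constant within a school, that is, a group contrast. A group-by-activity term fitted without the school level also ignores how the groups were formed. Its error depends in addition on how activity, and its relation to the outcome, vary between schools, so 1.68 is not its design effect. For the plain activity coefficient, the size and even the direction of the SE error depend on the within-school correlation of activity, and the figures do not carry over.

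**The case against.** Several counter-arguments have force.

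- **Social skills are already covered.** A reader might infer that both outcomes are compared between arms without clustering. The documents do not support that: social skills are on the effectiveness list and fall under the multilevel model. This objection stands, and it limits the point to self-concept and to the second regression.
- **The second regression asks a different question.** Its declared aim is how far activity contributes to the changes, so its main target is the activity coefficient, to which the figures above do not apply. This stands too. What remains is that the sentence extends to the comparison between groups, so group terms are within its scope.
- **Clustering may merely be unstated.** The text does not rule out a school term or cluster-robust standard errors, a condensed article may leave these to a fuller plan, and the general phrase about change from baseline could cover self-concept. This makes the conclusion conditional. It does not remove it, because the sentence names its own method and level in contrast to the multilevel model.
- **Teacher clustering.** It is tempting to argue that the scales rest mainly on teachers, each rating several children, so that the ICC must be well above 0.04. Table 1 does not support this. Social skills use "Parent and teacher reports", and the self-concept scale is given to the child as well as rated by the teacher. No number of teachers, no number of children per teacher and no teacher-level ICC is given. A stable school or rater effect would also cancel in a change score, so the relevant ICC could be lower.

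**Conclusion.** The point holds in a limited form. As written, the only analysis that names self-concept is an individual-level regression with no stated school level, although its results are to bear on the comparison of the arms. If it is run that way, a group contrast has a standard error about 23% too small and a type I error of about 13% instead of 5%.

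This rests on three assumptions: that the school level really is left out, that the ICC of 0.04 given for activity also serves for change in self-concept, and that there are 18 children per school. With assumed ICCs of 0.01 to 0.10 the error rate runs from about 7% to 23%.

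Nothing here shows that the planned test of the intervention on social skills is invalid or that the activity coefficient is too precise. A reader might also take that coefficient as showing how the intervention works. The protocol does not claim this, and the design would not support it: activity is not itself randomised, it is the trial's primary outcome, and its post-test value can be affected by allocation.

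**What to change.** Three changes of wording in Data analysis, or in the analysis plan if one exists:

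1. Add self-concept to the effectiveness outcomes and analyse its change between the arms with the same mixed-effects multilevel model as activity and social skills.
2. State that the regression on activity level keeps the school level, by a school random effect or by a cluster adjustment suited to only 12 clusters.
3. State that the activity coefficient will be reported as an association, not as a randomised contrast.

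No further data are needed, since each child's school is known. The cost is wider intervals: at an ICC of 0.04 and 18 children per school, the standard error of a group contrast is about 1.30 times the naive one. That is the precision the design actually provides.

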#### Process evaluation

During and after each round of data collection, the process is evaluated and the methods of data collection and communication are reassessed to monitor fidelity to the treatment. Teachers' and administrators' perceptions and attitudes are assessed by survey and informal interviews. Photos, videos and onsite observations of the school playgrounds are used to monitor and evaluate the progression of the use of unstructured materials.

## Discussion

Children's obesity, bullying and poor social skills represent a challenge to their mental and physical health. These three are often inter-related, but can be reversed. Many programs aiming at increasing physical activity have been implemented in the last decades, but most of them fail to have the potential to be adopted everywhere anywhere, due to structure, cost and lack of appeal to some children. This project is novel in investigating the benefits of free play on the playground for increasing physical activity and social skills in children and challenging adults to consider how their perceptions of risk may impact children's access to active free play. Due to its scope and potential to be adopted anywhere, if we have positive findings, this project has the prospect to influence policy around school-, and public playgrounds.
